### Sequence generation

Upon recruiting the schools and participants that fulfil the eligibility criteria, schools will be allocated to intervention or control groups using permuted block randomisation. The approach will ensure that closely balanced numbers of schools will be allocated to each study arm. Variable block sizes of 4, 6, and 8 will be used to blind the researcher from predicting the school allocation process.

### Allocation concealment

A randomisation list will be generated using “Create a block randomisation list” (Sealed Envelope Ltd., 2019). The main investigator will conduct the sequence generation and allocation concealment. Trained researchers will implement the study, which includes participant enrolment, envelope opening, and intervention administration in accordance with the CONSORT statement [21]. The list will include unique software-generated allocation codes consisting of two letters, followed by ≥ 1 digits (BW2, AM4, AB1, etc.). The codes will represent the intervention or control group. Only the sequence generator will be aware of the meaning of the codes to ensure allocation concealment. Subsequently, participants will be recruited using sequentially numbered, opaque, and sealed envelopes. The codes will be printed, cut out, and sealed in opaque envelopes. Subsequently, the envelopes containing the randomisation codes will be drawn by the liaison officer at each participating school. The randomisation codes will be released after schools are recruited for the study, which would occur following the completion of the baseline measurement. Thus, the parties involved during the randomisation will be blinded to the group to which the schools will be allocated before the codes are revealed.

### Blinding

This study will use single-blinding, where the participants will not be aware of their group status. Single-blinding aims to minimise performance bias (the Hawthorne effect), where the participant might alter their responses or behaviour if they are aware of their allocated group. It is not be possible to blind the field researcher, who will deliver the intervention module to the participants. Participant single-blinding is possible in this study, as the participants will not know whether they are receiving the intervention module or standard care. The intervention module is defined as the iDEAL module in addition to standard care, while standard care is defined as the current programme conducted by schoolteachers, district health offices, or local authorities. The intervention and control groups will receive standard care, as it is part of the dengue prevention and control programme established by the local health authorities.

## Research phase and tools

This research protocol details the development, implementation, and effectiveness measurement of the iDEAL module in improving the KAP, environmental cleanliness index, and dengue index among schoolchildren in Selangor and Kuala Lumpur. This study consists of three phases (Fig 2).

**Fig 2 pone.0302736.g002:**
[figure not shown]
The three phases of intervention module development (3P-IMD).

### Phase I: Needs assessment

The needs assessment of the intervention will be conducted through the combination approach of community diagnosis. The KAP regarding dengue prevention and control will be assessed using a literature review, survey, nominal group discussion (NGD), and focus group discussion (FGD) among subject matter experts (SME) and stakeholders. All information will be used for module development (Phase II) to design the delivery, content, and assessment method and media.

### Phase II: Intervention module development

The iDEAL module will be systematically designed and developed. Table 1 outlines the six steps of the intervention module development.

**Table 1 pone.0302736.t001:** The intervention module development procedure.

Step	Objective	Activities
1.	Prioritises the content and theory model	NGD and FGD among SME (Fuzzy Delphi method will be used to rank and prioritise)
2.	Develop draft intervention module	Development group Review committee
3.	Determine appropriate intervention method, media, and assessment	Development group Review committee SME (Fuzzy Delphi method will be used to rank and prioritise)
4.	Pilot testing or pilot project	Small-scale preliminary study conducted to evaluate: feasibility duration cost adverse events
5.	Module evaluation	Evaluation: Context, input, process, and product (CIPP)
6.	Intervention module refinement	Incorporate feedback from pilot training and module evaluation to finalise the intervention module

### Phase III: Implementation and effectiveness measurement

The final module will be implemented at the selected schools. A trained researcher will conduct the intervention to ensure standardisation, which will be optimised using a pre-recorded video, briefing, and serial supervision by the principal investigator throughout the intervention period. The intervention module effectiveness will be measured using validated self-administered questionnaires at T_0_, T_1_, T_2_, and T_3_.

## Questionnaire

The primary study outcome will be the KAP score, which is measured with validated self-administered questionnaires at T_0_, T_1_, T_2_, and T_3_ post-intervention. The questionnaire will be printed in English and Malay. Furthermore, the questionnaire is a new instrument that will be developed and validated based on various combinations of questionnaires on similar topics. The questionnaire will be divided into the following parts:

Part 1: Participants information, which consists of questions on socio-demographics, socio-economics, and dengue infection history;Part 2: Dengue prevention and control knowledge;Part 3: Dengue prevention and control attitude;Part 4: Dengue prevention and control practices.

The secondary study outcome will be the environmental cleanliness index and *Aedes* index, which trained researchers will measure using an observational checklist tool at T_0_, T_1_, T_2_, and T_3_ post-intervention.

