### Sample size estimation

The sample size was calculated based on the desired primary outcome, namely knowledge of dengue prevention and control. The sample size was calculated using the formula for testing the difference in proportions between two groups [20]. Adjustment for a 70% attrition rate established that the sample size required for this study is 800 pairs of intervention and control groups, which amount to 1600 participants.

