## Data analysis

The data analysis will involve the intention-to-treat analysis strategy. The approach analyses the results in a randomised study, where all randomised participants are included in the statistical analysis and analysed according to the group they were originally assigned, regardless of the treatment received.

The collected data will be analysed using IBM SPSS version 28 and descriptive and inferential statistics. Data exploration will be performed to identify data entry errors, missing data, and outliers. Subsequently, the numerical data will be identified as normally or non-normally distributed via statistical and graphical methods. The statistical method will involve calculating the skewness or standard error (SE) of skewness and the Kolmogorov-Smirnov parameter, while the graphical method will involve plotting and analysing histograms and stem and leaf box plots. Normally distributed data will be described using mean and standard deviation, while non-normally distributed data will be described using median and the first and third quartiles (Q1, Q3). Categorical data will be presented as frequency and percentage.

The hypothesis will be tested using a significance level with a p-value of 0.05 and a confidence interval of 95%. Results that yield a p-value < 0.05 will be considered statistically significant. For between-group comparisons, the mean difference of continuous and normally distributed data between the intervention and control groups will be compared using the independent sample *t*-test. For continuous but non-normally distributed data, the intervention and control groups will be compared using the Mann-Whitney U test. The frequency difference of categorical data between the intervention and control groups will be compared using the chi-square test. Fisher’s exact test will be used for data from 2 × 2 tables, which contain >20% cells with an expected count < 5.

Within-group changes over time will be compared using one-way repeated measure analysis of variance (ANOVA) for continuous and normally distributed variables. Cochran’s Q test will be used for within-group analysis of categorical data. The main effect and interaction between and within the intervention and control groups at T_0_, T_1_, T_2_, and T_3_ will be tested using the generalised linear mixed model (GLMM).

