## Supervisory committee

The supervisory committee will involve the researchers and stakeholders. The committee will monitor the study from its initiation to the end, monitor the data, and advise on the research methods and appropriateness regarding the study aims. Monthly meetings are planned, with supervisory committee members requested for further input, including trial conduct auditing, reviewing interim analysis results, and halting the guideline if needed.

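### The trial is sized on knowledge as a proportion, but the declared primary outcome is the three-part KAP score, so the plan does not fix which result decides the trial

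*Protocol article*

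**What the plan says.** Two sections of the protocol article define the primary outcome.

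- Sample size estimation: "The sample size was calculated based on the desired primary outcome, namely knowledge of dengue prevention and control". The method follows: "The sample size was calculated using the formula for testing the difference in proportions between two groups". The result is given as: "Adjustment for a 70% attrition rate established that the sample size required for this study is 800 pairs of intervention and control groups", that is, 1600 participants.
- Questionnaire: "The primary study outcome will be the KAP score, which is measured with validated self-administered questionnaires", at T0, T1, T2 and T3. The outcome parts are listed as "Part 2: Dengue prevention and control knowledge;Part 3: Dengue prevention and control attitude;Part 4: Dengue prevention and control practices". The section gives no rule for combining the three parts into one total, and no cut-off that would turn a score into a proportion.

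The Data analysis section sets one rule for all results: "Results that yield a p-value < 0.05 will be considered statistically significant". It lists between-group tests for continuous data (t-test, Mann-Whitney) and categorical data (chi-square, Fisher), and within-group tests (repeated-measures ANOVA, Cochran's Q). It also plans a GLMM, described as testing "The main effect and interaction between and within the intervention and control groups at" the four time points. None of these is named as the test that decides the trial.

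**The concern.** The primary outcome governs the sample size, the use of the 5% error rate and the trial's headline conclusion. Here the two statements differ in construct (one domain against three) and, as far as the text shows, in scale (a proportion against a score). A statistician who follows the Sample size estimation section would report knowledge. One who follows the Questionnaire section would report KAP, as a total or as three domains.

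Two things are at stake. The number of participants is not tied to the outcome declared primary. And with a blanket 0.05 rule, a significant difference in knowledge, in attitude, in practice or in a total could each be presented as meeting the primary objective.

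**Working it through.** **The plan's own figure.** 2 × 800 = 1600 agrees with the stated total. The 800 per arm cannot be rebuilt, because the article does not give the two proportions or the power. An article may leave those to a fuller document, so this is not part of the point. The figure before attrition depends on how the 70% is read:

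- 800 × (1 − 0.70) = 240 per arm
- 800 / 1.70 ≈ 470 per arm
- 800 × 0.70 = 560 per arm (if 70% are retained)

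Whichever is meant, the calculation described is for knowledge as a proportion. Nothing in it refers to attitude, to practice or to a combined score.

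**The two definitions side by side.**

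| | Sample size estimation | Questionnaire |
|---|---|---|
| Primary outcome | Knowledge | KAP score |
| Domains | One | Three |
| Scale | Proportion | Score, scaling not stated |
| Time point | Not stated | T0, T1, T2, T3, none ranked first |

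**Size of the multiplicity.** Inputs: 0.05 per test (Data analysis; two-sided assumed), three domains and three follow-up visits (Questionnaire). Assumption: any one significant result would count as primary success; the document sets no rule that all must be significant. For k independent tests, the chance of at least one false positive is 1 − 0.95^k.

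- One composite score, tested by a GLMM main effect and an interaction (k = 2): 1 − 0.95² = 9.75% at most.
- One test per domain (k = 3): 1 − 0.95³ = 14.3%. Simulation with assumed between-domain correlations of 0.3 to 0.7 gives 13.6% to 10.9%.
- Three domains each tested separately at three visits (k = 9): 1 − 0.95⁹ = 37.0%. Simulation with assumed correlations of 0.3 to 0.7 between domains and 0.3 to 0.8 between visits gives about 34% down to 21%.

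These figures count false positives in either direction. Counting only those that favour the module, nine independent tests give 1 − 0.975⁹ = 20.4%.

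**The case against.** The strongest reply has four parts.

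1. *Knowledge is one part of KAP, so this is a part against its whole and not two unrelated endpoints.* True, but the primary outcome must still be one or the other. If KAP is a single composite, the trial remains sized on a different outcome from the one declared.

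2. *The text does not plan nine tests.* This stands. A reader might infer a test of each domain at T1, T2 and T3, but the Data analysis section names the time points only for the GLMM and ties the t-test and its alternatives to no follow-up visit. The Questionnaire section speaks of one KAP score, and a single group-by-time test could cover all visits. So 37% is a conditional ceiling, not a description of the plan.

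3. *Multiplicity rules, the testing order and the deciding model term are commonly left to an analysis plan.* This also stands, and their absence alone would be no finding. A reader might infer that the GLMM group main effect decides efficacy, but the article lists it with the interaction and ranks neither. A reader might also infer repeated efficacy looks from the Supervisory committee's possible task of "reviewing interim analysis results, and halting the guideline if needed". No between-arm efficacy look is described, so none can be charged with raising the error rate.

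4. *A proportion-based sample size need not conflict with the analysis.* Partly right. Chi-square, Fisher and Cochran's Q are planned, and a GLMM can model a binary outcome. It would go too far to say that the sample size supports none of the planned tests. But the article declares a score and gives no categorisation, so the match between scale and formula is left open.

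**Conclusion.** The contradiction holds on the article's own text: the Sample size estimation and Questionnaire sections name different primary outcomes. No unseen analysis plan is needed to show it, and it has to be reconciled. With the blanket 0.05 rule, more than one result could be claimed as primary success.

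The size depends on how the score is used. If any one significant result counts, the chance of a false positive is up to 9.75% for one composite tested in two ways and up to 14.3% for one test per domain. The 37% figure is an upper bound that needs nine separate, independent tests and counts both directions. Correlation between domains or visits lowers all of these, and the correlations used above are assumed.

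**What to change.** Make the Sample size estimation and Questionnaire sections name the same single primary outcome. Knowledge is the natural choice, because the trial was sized on it.

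- **Scale.** State a scale that matches the sample size formula. Either define the proportion (the cut-off for adequate knowledge), or use a mean score and restate the basis of the sample size.
- **Contrast.** Name one between-arm GLMM contrast at one follow-up, chosen by the sponsor before any between-arm results are seen. Enter T0 as a covariate, or express the contrast as a change from T0. A group main effect averaged over T0 to T3 should not serve. The Allocation concealment section releases the codes after baseline, so T0 can carry no effect, and with equal weights a constant later effect d would be estimated as (0 + d + d + d)/4 = 0.75d.
- **Everything else.** Make attitude, practice and the other visits secondary, tested in a fixed order after the primary.

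**Cost.** Attitude and practice lose primary status. If knowledge stays a proportion, the change is wording plus a cut-off. If a mean score is chosen, it is more than wording: the questionnaire is still to be developed, the article gives no standard deviation, and the required number could change.

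Keeping three co-primary domains with any one sufficient is possible but dearer. Bonferroni gives 0.05/3 = 0.0167 per test. At an assumed 80% power and a fixed effect, the required number rises by ((2.394 + 0.842)/(1.960 + 0.842))² = 1.33. If the number is kept, power per test falls from 80% to 66%.

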## Validity and reliability

The content validity of the questionnaire will be assessed by SME, which will include a public health medicine specialist, family medicine physicians, health educators, health promoters, and school teachers from various agencies. The questionnaire acceptability will be assessed by calculating the content validation ratio (CVR). Furthermore, the SME comments and feedback will be considered for further correction of the questionnaire. Additionally, the assigned experts will assess the questionnaire relevance and clarity by calculating the content validity index (CVI). Subsequently, the Item CVI (I-CVI) and the scale average CVI (S-CVI/Ave) will be calculated. The questionnaire will be modified according to the experts’ agreement level based on the calculated CVI. Face validation among the schoolchildren will be conducted to ensure their accurate understanding of the meaning underlying each item and the feasibility of the data collection period.

The instrument reliability will be measured using the internal consistency method calculated in IBM Statistical Package for Social Science (SPSS) version 28. The sample size for the instrument reliability study will be calculated using a web-based sample size calculator (https://wnarifin.github.io/ssc_web.html). Subsequently, participants will be recruited to achieve the sample size. All participants recruited for the instrument reliability test will be excluded from the main study. The internal consistency of the scale will be calculated using Cronbach alpha coefficient (a Likert scale) or Kuder-Richardson coefficient (items with a dichotomous response).

## Data collection

Upon initiating the study, the liaison officer will obtain consent from the students who fulfil the eligibility criteria. Subsequently, T_0_ data will be obtained from the students who consent to participate in the study. The participants allocated to the intervention group will be given appointments within one month for intervention package delivery according to class. The total duration of the intervention sessions will be approximately 30 minutes in three meetings. After completing the intervention, the participants will be required to answer the post-intervention assessment measuring the study outcome at T_1_, T_2_, and T_3_. The control group will undergo the same assessment as the intervention group at T_0_, T_1_, T_2_, and T_3_. Fig 3 depicts the study flow diagram based on the CONSORT 2010 statement [20].

**Fig 3 pone.0302736.g003:**
[figure not shown]
Flow diagram of study based on the CONSORT statement.

## Data analysis

The data analysis will involve the intention-to-treat analysis strategy. The approach analyses the results in a randomised study, where all randomised participants are included in the statistical analysis and analysed according to the group they were originally assigned, regardless of the treatment received.

The collected data will be analysed using IBM SPSS version 28 and descriptive and inferential statistics. Data exploration will be performed to identify data entry errors, missing data, and outliers. Subsequently, the numerical data will be identified as normally or non-normally distributed via statistical and graphical methods. The statistical method will involve calculating the skewness or standard error (SE) of skewness and the Kolmogorov-Smirnov parameter, while the graphical method will involve plotting and analysing histograms and stem and leaf box plots. Normally distributed data will be described using mean and standard deviation, while non-normally distributed data will be described using median and the first and third quartiles (Q1, Q3). Categorical data will be presented as frequency and percentage.

The hypothesis will be tested using a significance level with a p-value of 0.05 and a confidence interval of 95%. Results that yield a p-value < 0.05 will be considered statistically significant. For between-group comparisons, the mean difference of continuous and normally distributed data between the intervention and control groups will be compared using the independent sample *t*-test. For continuous but non-normally distributed data, the intervention and control groups will be compared using the Mann-Whitney U test. The frequency difference of categorical data between the intervention and control groups will be compared using the chi-square test. Fisher’s exact test will be used for data from 2 × 2 tables, which contain >20% cells with an expected count < 5.

Within-group changes over time will be compared using one-way repeated measure analysis of variance (ANOVA) for continuous and normally distributed variables. Cochran’s Q test will be used for within-group analysis of categorical data. The main effect and interaction between and within the intervention and control groups at T_0_, T_1_, T_2_, and T_3_ will be tested using the generalised linear mixed model (GLMM).

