**Methods:**

This study is a single-blinded, cluster randomised controlled trial to be conducted from 1 September 2023 to 31 August 2025. The study will involve 20 primary and 20 secondary schools in Selangor and Kuala Lumpur. The 1600 participants will be randomly allocated to intervention and control groups based on selected clusters to avoid contamination. A cluster is a comparable school that fulfils the inclusion and exclusion criteria. The intervention group will receive the iDEAL module, while the control group will receive standard education. The iDEAL module will be developed following a systematic procedure and delivered in-person by trained researchers to the participants. The outcome will be measured using validated, self-administered questionnaires at baseline (T_0_), immediately (T_1_), one month (T_2_), and three months (T_3_) post-intervention to measure the intervention module effectiveness. The data will be analysed using IBM Statistical Package for Social Science (SPSS) version 28 and descriptive and inferential statistics. Within-group changes over time will be compared using one-way repeated measure analysis of variance for continuous and normally distributed variables. Within-group analysis of categorical data will use Cochran’s Q test. The main effect and interaction between and within the intervention and control groups at T_0_, T_1_, T_2_, and T_3_ will be tested using the generalised linear mixed model (GLMM). Hypothetically, the KAP, environmental cleanliness index, and dengue index among the intervention group will be significantly improved compared to the control group. The hypothesis will be tested using a significance level with a p-value of 0.05 and a confidence interval of 95%.

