The authors intend to develop, implement, and evaluate the effectiveness of a theory-based integrated dengue education and learning (iDEAL) module in improving the KAP, environmental cleanliness index, and dengue index among schoolchildren in Selangor and Kuala Lumpur. The specific objectives are to develop the iDEAL module, determine and compare the baseline sociodemographic, socioeconomic, and dengue infection history between intervention and control groups, and evaluate the within- and between-group effects of the iDEAL module in improving the KAP, environmental index, and dengue index at baseline (T_0_), immediately (T_1_), one month (T_2_), and three months (T_3_) post-intervention.

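### Student-level t, Mann-Whitney, chi-square and Fisher tests are prescribed for arm comparisons although 40 schools are randomised, so for the KAP outcomes they do not hold the 5% level

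*Protocol article*

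**What the plan says.** The abstract's Methods paragraph states the design: "This study is a single-blinded, cluster randomised controlled trial to be conducted from 1 September 2023 to 31 August 2025". It gives the number of clusters: "The study will involve 20 primary and 20 secondary schools in Selangor and Kuala Lumpur". Under Sequence generation, "schools will be allocated to intervention or control groups using permuted block randomisation". One classroom is drawn per school (Sampling method and participant recruitment), so school and class are the same cluster in practice. The planned total is 1600 students (Sample size estimation).

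The Data analysis section sets significance at p < 0.05 and then lists tests for comparing the arms. For normally distributed variables, "the mean difference of continuous and normally distributed data between the intervention and control groups will be compared using the independent sample" t-test. For non-normal variables, "the intervention and control groups will be compared using the Mann-Whitney U test". Categorical data get the chi-square test, or Fisher's exact test when the table is sparse. None of these is limited to baseline or to description.

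For change inside each arm, "Within-group changes over time will be compared using one-way repeated measure analysis of variance (ANOVA) for continuous and normally distributed variables", with Cochran's Q for categorical data. The objectives in the Introduction are to "evaluate the within- and between-group effects of the iDEAL module" at the four assessment times.

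A GLMM is named last in the Data analysis section, for main effects and the interaction over T0 to T3. The section does not say which analysis decides effectiveness.

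**The concern.** The listed between-arm tests take every student as an independent observation. Students in one class share teachers, a neighbourhood and, in the intervention arm, the same delivery sessions, so their scores are likely to be correlated. Because whole schools are allocated, that correlation goes straight into the difference between arms. A student-level test leaves it out of the standard error, so p-values come out too small and confidence intervals too narrow. KAP is the primary outcome and is measured on students, so a false positive there would be a false positive for the trial. The Data sharing section plans nationwide use of the module.

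The second issue is one of interpretation. Both arms answer the questionnaire four times (Data collection) and both receive standard care (Blinding). Scores can rise in the intervention arm through retesting or standard care alone. A significant change within that arm therefore says nothing about the module, although the objectives describe within-group results as its effects.

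**Working it through.** **Inputs from the protocol.** 40 schools, allocated 1:1, so about 20 per arm; 1600 students; one class per school; significance at p < 0.05 (sidedness not stated, taken as two-sided); 70% attrition, taken as written.

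**Cluster size.** m = 1600/40 = 40. With 70% attrition, 1600 × 0.30 = 480 students remain, and 480/40 = 12 per school.

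**Assumption.** The documents give no ICC. Values from 0.01 to 0.10 are assumed here. The ICC that matters is that of whatever quantity is compared between arms.

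**Formulas.** Design effect DE = 1 + (m − 1) × ICC. True two-sided type I error of a student-level test = 2 × [1 − Φ(1.96/√DE)].

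**The plan's own figure.** At ICC = 0, DE = 1 and the formula returns 5.0%. Simulation with 40 per school gave 4.8% to 5.0% across the t-test, Mann-Whitney and chi-square tests. The nominal 5% is thus reproduced only if students are independent.

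**With clustering.**

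| ICC (assumed) | DE, m = 40 | Type I error, m = 40 | DE, m = 12 | Type I error, m = 12 |
|---|---|---|---|---|
| 0.01 | 1.39 | 9.6% | 1.11 | 6.3% |
| 0.02 | 1.78 | 14.2% | 1.22 | 7.6% |
| 0.05 | 2.95 | 25.4% | 1.55 | 11.5% |
| 0.10 | 4.90 | 37.6% | 2.10 | 17.6% |

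Example: m = 40 and ICC 0.05 give DE = 1 + 39 × 0.05 = 2.95 and 1.96/√2.95 = 1.14, hence 25.4%.

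**Check by simulation** (20 equal-sized schools per arm, no true effect, 4000 runs; the chi-square test used the score split at its midpoint).

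| m | ICC | t-test | Mann-Whitney | Chi-square | t-test on school means |
|---|---|---|---|---|---|
| 40 | 0.01 | 9.4% | 9.2% | 8.1% | 4.7% |
| 40 | 0.05 | 24.7% | 24.1% | 18.7% | 4.8% |
| 40 | 0.10 | 39.0% | 37.7% | 29.7% | 5.0% |
| 12 | 0.05 | 12.1% | 11.8% | 9.7% | 5.3% |
| 12 | 0.10 | 16.9% | 16.3% | 12.6% | 5.0% |

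The t-test and Mann-Whitney results agree with the formula. Chi-square is somewhat lower because the ICC was set on the underlying score and splitting the score weakens it. Fisher's exact test was not simulated. A test on 20 against 20 school means holds the level.

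**Within-arm repeated-measures ANOVA** (20 schools, four visits, 3000 runs). If schools differ only by a constant level, the error is 4.4% to 5.0% with 40 per school: the school effect cancels. If school-by-time variance is 1%, 2% or 5% of the total, the error is 20%, 36% or 65% with 40 per school, and 8%, 12% or 28% with 12.

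**The case against.** The strongest reply is that the GLMM is the real effectiveness analysis. The abstract omits the t-test, Mann-Whitney and chi-square tests and names the GLMM for comparing the arms, and the Discussion and conclusion ties the hoped-for improvement to the GLMM. One stated objective is to compare baseline characteristics between arms, which the simple tests could serve. This makes the role of the simple tests ambiguous, and a reader should not infer that they are certain to decide the result. But the Data analysis section offers them for between-group comparisons in general, at the same significance threshold, and never ranks them below the GLMM. An analyst following the text could report them as effectiveness tests.

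It is also fair that the GLMM's random effects and the handling of missing visits are ordinary content of an analysis plan that is not shown. The absence of a stated school effect is therefore not counted as a fault. For the same reason, a reader might see a contradiction between repeated-measures ANOVA, which usually drops students with a missed visit, and the intention-to-treat rule, "where all randomised participants are included in the statistical analysis". The article does not specify a complete-case analysis, so that contradiction is not established.

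Two further readings fail. Clustering by itself does not inflate the within-arm tests, as the simulation shows; schools must differ in their change over time. And the Kolmogorov-Smirnov statistic is not the sole route to choosing a test, because skewness and plots are used too.

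Finally, the ICC is assumed. With a very low ICC and small classes (0.01 and 12 per school) the error is only 6.3%.

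**Conclusion.** The point stands for student-level KAP outcomes. As prescribed, the between-arm t-test, Mann-Whitney and chi-square tests do not hold 5% at any positive ICC, and Fisher's exact test rests on the same independence assumption. For the t-test, the true error is about 10% to 38% for ICC 0.01 to 0.10 with 40 per school, and about 6% to 18% with 12 per school. This rests on the assumed ICC range, equal cluster sizes and a two-sided test.

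Separately, neither repeated-measures ANOVA nor Cochran's Q within an arm can show an effect of the module. That is a matter of interpretation and does not depend on the ICC. Inflated error in those tests arises only if schools differ in change over time. That is plausible, since the module is delivered class by class, but the documents give no figure for it.

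The conclusion does not automatically extend to the environmental cleanliness and Aedes indices. Researchers record these with a checklist and the unit is not stated. If there is one value per school, a test on 40 school values is valid.

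**What to change.** In the Data analysis section:

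- Limit the t-test, Mann-Whitney, chi-square and Fisher's exact tests to descriptive use for student-level data.
- State that the effectiveness conclusion for KAP rests on the between-arm (arm-by-time) contrast from the GLMM, with random effects for school (preferably including school-by-time) and for student, small-sample degrees of freedom, and all available assessments.
- Report within-arm changes as descriptive estimates from that model, and reword the objective so that they are not called effects of the module.
- State the unit of the environmental and Aedes indices. If they are recorded once per school, analyse them at school level.

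Only the wording of the analysis changes; design and data collection stay as they are. Intervals will be wider than those from student-level tests, by a factor of √DE: at an assumed ICC of 0.05, √2.95 ≈ 1.72 with 40 per school and √1.55 ≈ 1.24 with 12. A test on school means held the level in simulation. The GLMM addresses the same problem but was not itself simulated.
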